## Abstract

**Background:**

Chronic kidney disease (CKD) is characterized by dysbiosis, elevated levels of uremic toxins, systemic inflammation, and increased markers of oxidative stress. These factors lead to an increased risk of cardiovascular disease (CVD) which is common among CKD patients. Supplementation with high amylose maize resistant starch type 2 (RS-2) can change the composition of the gut microbiota, and reduce markers of inflammation and oxidative stress in patients with end-stage renal disease. However, the impact of RS-2 supplementation has not been extensively studied in CKD patients not on dialysis. Aerobic exercise training lowers certain markers of inflammation in CKD patients. Whether combining aerobic training along with RS-2 supplementation has an additive effect on the aforementioned biomarkers in predialysis CKD patients has not been previously investigated.

**Methods:**

The study is being conducted as a 16-week, double-blind, placebo controlled, parallel arm, randomized controlled trial. Sixty stage 3–4 CKD patients (ages of 30–75 years) are being randomized to one of four groups: RS-2 & usual care, RS-2 & aerobic exercise, placebo (cornstarch) & usual care and placebo & exercise. Patients attend four testing sessions: Two baseline (BL) sessions with follow up visits 8 (wk8) and 16 weeks (wk16) later. Fasting blood samples, resting brachial and central blood pressures, and arterial stiffness are collected at BL, wk8 and wk16. A stool sample is collected for analysis of microbial composition and peak oxygen uptake is assessed at BL and wk16. Blood samples will be assayed for p-cresyl sulphate and indoxyl sulphate, c-reactive protein, tumor necrosis factor α, interleukin 6, interleukin 10, monocyte chemoattractant protein 1, malondialdehyde, 8-isoprostanes F2a, endothelin-1 and nitrate/nitrite. Following BL, subjects are randomized to their group. Individuals randomized to conditions involving exercise will attend three supervised moderate intensity (55–65% peak oxygen uptake) aerobic training sessions (treadmills, bikes or elliptical machine) per week for 16 weeks.

**Discussion:**

This study has the potential to yield information about the effect of RS-2 supplementation on key biomarkers believed to impact upon the development of CVD in patients with CKD. We are examining whether there is an additive effect of exercise training and RS-2 supplementation on these key variables.

**Trial registration:**

Clinicaltrials.gov

**Trial registration#**
NCT03689569.

9/28/2018, retrospectively registered.

## Background

Cardiovascular disease (CVD) is the major cause of death among patients with chronic kidney disease (CKD) [1]. This increased risk of CVD is linked to the accumulation of uremic toxins, derived from abnormal bacterial growth within the gut (Rossi, Johnson, Morrison, Pascoe, & Jeff, 2018). Furthermore, CKD is marked by systemic inflammation and high levels of oxidative stress [2–4]. High levels of inflammation and oxidative stress are both thought to be key factors in the progression of CKD and in the development of CVD among patients with CKD [5, 6]. The uremia found in CKD patients is believed to damage the tight junctions between epithelial cells in the intestinal walls resulting in a more porous gut barrier, allowing toxins from the gut microbiota to leak into the systemic circulation of CKD patients. This would normally be prevented in healthy individuals by an impenetrable gut barrier. These enterotoxins trigger an immune response, which results in a heightened state of inflammation [5, 6].

CKD patients are typically prescribed diets to restrict the intake of potassium and phosphorus; this restriction leads to a reduction in the consumption of soluble fiber, which is known to have several health benefits [7–9]. There is evidence from both animal and human studies, primarily in persons with end-stage renal disease (ESRD), that supplementation with high amylose maize resistant starch type 2 (RS-2), a prebiotic, leads to a reduction in inflammation and oxidative stress [10–12]. Certain strains of beneficial bacteria utilize resistant starch as a nutrient to produce short chain fatty acids (acetate, propionate, and butyrate), which serve as nutrients for intestinal epithelial cells, promoting the repair of the altered tight junctions and aiding in the reduction of harmful bacteria [10, 12]. Consequently, fewer microbial components leak through the intestinal epithelium and enter the systemic circulation and the inflammatory response is reduced [10]. This effect has been demonstrated in a group of ESRD patients following an 8 week period of supplementation with RS-2 following which there was an increase in faecalibacterium, an anti-inflammatory gut microbe found at high levels in healthy individuals but reduced in a number of human diseases,and a reduction in both uremic toxins and markers of inflammation [11].

As demonstrated by Laffin et al. [11], supplementation with RS-2 leads to a reduction in uremic toxins in CKD patients. Key uremic toxins include indoxyl sulphate (IS) and p-cresyl sulphate (PCS) which are believed to accumulate systemically in CKD patients due to increased metabolism of some amino acids (tryptohan and tyrosine) and the kidney’s impaired ability to remove these substances [4, 13]. The accumulation of these uremic toxins also disrupts the balance between markers of inflammation and oxidative stress, which ultimately creates conditions that facilitate endothelial dysfunction and rapid atherosclerosis [4].

There is strong evidence that chronic levels of increased physical activity lead to reductions in systemic markers of inflammation: c-reactive protein (CRP), interleukin 6 (IL-6) and tumor necrosis factor alpha (TNF-α) that correlate with changes in gut microbes [14–16]. However, acute exercise leads to a marked transient increase in IL-6 concentrations which is believed to have an anti-inflammatory effect by increasing the anti-inflammatory cytokines IL-1 receptor antagonist (IL-1RA) and interleukin 10 (IL-10) and decreasing the pro-inflammatory cytokine TNFα [17]. IL-6 brings about these favorable changes in the inflammatory milieu via actions on monocytes and macrophages [16]. Chronic exercise training protects against low grade systemic inflammation implicated in the development of many non-communicable diseases [16]. Elevated levels of IL-6, at rest, have been associated with a greater risk of premature mortality in CKD patients [3]. Chronic moderate intensity aerobic exercise decreases resting levels of IL-6 while at the same time increasing IL-10 levels [3].

The impact of resistant starch, primarily RS-2, has been primarily demonstrated in hemodialysis patients [11]. There have been few, if any, reported studies of the impact of RS-2 in CKD patients not on dialysis on the aforementioned biomarkers. Other forms of prebiotics (e.g. fructans) have been investigated with varying effects [13]. Therefore, the primary aim of this study is the examine the impact of 16 weeks of supplementation with RS-2, in association with aerobic exercise training, in a sample of stage 3–4 CKD patients on markers of inflammation, oxidative stress, uremic toxins and on the composition of the gut microbiota. Our proposal is novel in that it attempts to address one of the root causes of the elevated inflammation in CKD patients (dysfunctional microbiome) and determine whether moderate aerobic exercise training, which has been shown to have anti-inflammatory effects in some studies with CKD patients, has an additive effect along with RS-2 supplementation.

We hypothesize that supplementation with RS-2 will lead to normalization of the composition of the microbiota in our sample of CKD patients and reduce key markers of inflammation, oxidative stress, and uremic toxins. Reductions in these biomarkers will be associated with favorable changes in cardiovascular variables (arterial stiffness, blood pressure and vasoactive substances). We also hypothesize that moderate intensity aerobic training will have an additive anti-inflammatory effect along with the consumption of the resistant starch. The study is being conducted as a double-blind, placebo controlled, parallel arm randomized clinical trial.

## Methods/design

### Study setting

The study is being conducted at an academic institution in association with a local nephrology practice. The study has been reviewed and approved by the Institutional Review Board of the academic institution. This Board assumes the responsibility for monitoring the study. Any adverse events are required to be reported to the IRB in compliance with policies of this Board. Any changes to the original protocol are reviewed and approved by the IRB before implementation in this study. If additional analyses are to be performed that are not listed in the original consent form, consent will be required prior to performing any new analyses.

### Eligibility criteria

#### Inclusion criteria

Sixty stage 3–4 CKD (GFR 15–59 ml/min/m^2^) patients between the ages 30–75 years are being recruited for this study, which is being completed over a 3-year period. Other inclusion criteria include the ability of the individual to comply with all aspects of the study protocol and to be able to give consent independently.

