#### Testing sessions and timeline

Participants are asked to attend a total of four testing sessions (see Fig. 1), all conducted at the academic institution’s Human Performance Laboratory. During the first visit, anthropometric variables of, height (Detecto, Webb City, Missouri), weight and body composition via bioelectrical impedance (BC-418,Tanita,Tokyo, Japan) are assessed along with the determination of peak oxygen uptake (VO_2peak_) using a computerized metabolic cart (MAX-II, AEI Technologies, Pittsburg, PA), that is calibrated according to manufacturer’s specifications. The cardiopulmonary exercise test is performed on a motor driven treadmill with a Q-stress system (Welch Allyn, Skaneateles Falls, NY) using the Modified Bruce protocol. Resting cardiovascular (CV) variables (i.e., central and peripheral blood pressure, pulse wave velocity and pulse wave analysis) are assessed using applanation tonometry (SphygmoCor Excel, AtCor Medical Inc., Itasca, IL) after a 10-min rest period in the supine posture. One week later, patients return to the Human Performance Laboratory for their second baseline visit following at least an 8-h fast. On arrival, a blood sample is taken, and processed by spinning in a refrigerated centrifuge (4 °C, and spun at 3000 rpms for 15 min). The plasma is then removed and placed in 10 storage tubes and stored in a − 80° freezer for later analysis. Prior to visit 2, participants collect a stool sample at home and complete a 3-day food record documenting the brand, portion size, and preparation methods of all foods and beverages consumed. Both the stool sample and the food records are brought to the lab for visit 2. Following baseline testing, subjects are assigned randomly to one of 4 groups ensuring equal number of subjects in each group: Group A receives the prebiotic supplement with usual care but no prescribed exercise, Group B receives the prebiotic supplement and performs supervised aerobic exercise training at a moderate intensity for 16 weeks, Group C receives the placebo (cornstarch) supplement along with 16 weeks of moderate intensity aerobic exercise training, while group D receives the usual care and the placebo but no supervised exercise training. The randomization was performed by the study statistician prior to the start of the study.

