### Statistical analyses

An Intention-To-Treat design will be used in this study. Effects of treatment on all dependent variables will be assessed by a 2 (prebiotic supplement or control) by 2 (aerobic exercise or control) by 3 (time) mixed factor ANOVA. The effect of the prebiotic supplement will be determined by examining the prebiotic supplement x time interaction, the effect of exercise will be determined by examining the aerobic exercise x time interaction, and the combined effect of the supplement and exercise will be determined by examining the 3-way supplement x exercise x time interaction. Significant interactions will be explored through simple effects analysis. The main variables of interest are inflammatory markers, particularly IL-6, and IL-10.

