All other aspects of the protocol remain in place. There are no plans to resume the exercise components of this particular study. Additional modification will be needed for the statistical analyses. Given the reduced number of participants completing the exercise portion of the protocol, the intended comparison between the prebiotic and exercise conditions will only be exploratory in nature. The effect of the prebiotic compared to placebo will be examined by a 2 (prebiotic vs. placebo) × 3 (time) mixed factor ANOVA.

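### Qualifying GFR spans a 3.9-fold range but is absent from the stated RS-2 v placebo model; pre-specifying it with a time interaction is a cheap gain in precision, at least for PCS and IS

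*Protocol article*

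**What the plan says.** - **Entry (Inclusion criteria).** "Sixty stage 3–4 CKD (GFR 15–59 ml/min/m^2^) patients between the ages 30–75 years are being recruited". This is the only place in the article where a GFR value appears.
- **Why GFR matters (Background).** The article gives two causes for the build-up of IS and PCS: increased metabolism of certain amino acids, and "the kidney’s impaired ability to remove these substances [4, 13". The Outcomes section lists PCS and IS among the primary outcomes.
- **Allocation (Testing sessions and timeline).** "subjects are assigned randomly to one of 4 groups ensuring equal number of subjects in each group", and "The randomization was performed by the study statistician prior to the start of the study". No balancing factor other than group size is named.
- **Analysis (Statistical analyses).** The factorial plan is a "2 (prebiotic supplement or control) by 2 (aerobic exercise or control) by 3 (time) mixed factor ANOVA", and "The effect of the prebiotic supplement will be determined by examining the prebiotic supplement x time interaction".
- **Analysis after exercise was dropped (Update).** "The effect of the prebiotic compared to placebo will be examined by a 2 (prebiotic vs. placebo) × 3 (time) mixed factor ANOVA". The same section says that the analyses still need further modification.

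Neither model has a covariate.

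**The concern.** A patient at the bottom of the entry range has about a quarter of the GFR of one at the top. On the article's own account, kidney removal affects how much PCS and IS accumulate. Each patient's GFR has to be known before enrolment, yet the stated models do not use it.

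If GFR also predicts how the toxins change over 16 weeks, two things follow. Variation that the model could explain stays in the error term, so the RS-2 comparison is less precise than it need be. And in a trial of 60, a chance difference in GFR between the arms goes unadjusted. If the covariate is first added after the data have been seen by group, the choice is open to the charge of being data-driven. The plan is already being rewritten, so now is the time to settle it.

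**Working it through.** **Inputs from the article:** GFR 15 to 59; 60 participants, 15 in each of four groups; three time points; medium effect, power .80, alpha .05.

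**Assumptions, not in the article:** 30 v 30 for RS-2 v placebo (2 × 15 per supplement); d = 0.5 as medium; two-sided alpha; the correlation r between GFR and change in outcome; the share of stage 4 patients.

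**1. The plan's own figure.** I took the within-between interaction with noncentrality λ = f²·N·m/(1 − ρ), m = 3, f = 0.25 and sphericity. For 80% power the required total is:

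| Groups | ρ = 0 | ρ = 0.3 | ρ = 0.5 |
|---|---|---|---|
| 2 | 53 | 38 | 28 |
| 4 | 76 | 55 | 40 |

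The stated 60 lies within this spread, but the article gives neither ρ nor the conversion from d to f. The figure can be neither confirmed nor refuted, and this point does not depend on it.

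**2. Range.** 59/15 = 3.93.

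**3. What the test removes.** If GFR only shifts a patient's level, it adds b·GFR at every visit. In the change from baseline this becomes b·GFR − b·GFR = 0. If its effect differs by visit (b₀ at baseline, b₁₆ at week 16), then (b₁₆ − b₀)·GFR remains in the change. Only this second part matters for the supplement-by-time test.

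**4. Precision.** For one change score, the normal approximation gives power = Φ(d / [√(1 − r²)·√(2/n)] − 1.96). With n = 30, √(2/30) = 0.258 and 0.5/0.258 = 1.936.

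| r | √(1 − r²) | Φ argument | Power |
|---|---|---|---|
| 0 | 1.000 | 1.936 − 1.960 = −0.024 | 49% |
| 0.2 | 0.980 | 1.976 − 1.960 = 0.016 | 51% |
| 0.3 | 0.954 | 2.030 − 1.960 = 0.070 | 53% |
| 0.5 | 0.866 | 2.236 − 1.960 = 0.276 | 61% |

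The 49% is a reference point for a single change score. It is not the power of the planned three-time-point test.

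**5. Chance imbalance, if allocation is not stratified.** The standard error of a standardized baseline difference is 0.258, so the chance that mean GFR differs by more than 0.5 SD is 2·[1 − Φ(0.5/0.258)] = 5.3%. In head counts (hypergeometric, 60 patients, 30 per arm), the chance that the arms differ by at least 6 stage 4 patients is 10%, 16%, 17% and 19% if 12, 18, 20 or 24 of the 60 are stage 4.

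**6. What such an imbalance would do.** Six of 30 is 20 percentage points. If stage 4 and stage 3 patients differed by 0.5 SD in change, the contrast would shift by 0.2 × 0.5 = 0.10 SD. At 0.2 SD it would shift by 0.2 × 0.2 = 0.04 SD. The standard error of the contrast is 0.258 SD.

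**7. Form of the covariate.** In a mixed ANOVA the supplement-by-time effect is tested within patients. A GFR main effect explains only between-patient variation in average level, so it would leave that test essentially unchanged. The model needs GFR × time, or an equivalent adjustment of the follow-up values.

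**8. Unit.** The criterion is printed per m². The usual reference area for staging is 1.73 m² (not given in the article). Read literally, the printed range would be 15 × 1.73 = 26 to 59 × 1.73 = 102 per 1.73 m², which does not fit the stage named in the same sentence.

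**The case against.** The strongest reply is that an unadjusted randomized comparison is valid, and that an article may leave covariates and stratification to a fuller document. For stratification this stands: the article names no factor, but it does not say that the list was unstratified. For the analysis it stands only in part. The article states the model twice, once in a section written to revise it, and neither statement has a covariate. An unseen analysis plan could still add one.

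Four stronger readings are tempting and are not supported:

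- **That kidney function drives these outcomes.** The Background names impaired removal as one of two causes. That bears on toxin level. Nothing in the article shows that GFR predicts 16-week change or response to RS-2.
- **That the 10–19% is the risk of a wrong conclusion.** It is the chance of a head-count imbalance. The test's nominal error rate already allows for chance imbalance, and the shifts in step 6 of the working are well below one standard error.
- **That the trial admits near-normal kidney function.** The same sentence limits entry to stage 3–4, and patients are screened from a nephrology practice's database. Nothing suggests that anyone applied 26–102. The missing 1.73 is clerical.
- **That the whole primary analysis is affected.** PCS and IS are two of ten listed primary outcomes. The Statistical analyses section singles out IL-6 and IL-10, for which the article offers no link to GFR.

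**Conclusion.** The point holds as a modest, inexpensive improvement to a stated model. It does not show bias or invalidity. Entry covers a 3.9-fold GFR range, the article ties kidney removal to two primary outcomes, and the supplement-by-time models leave out a baseline value that eligibility requires.

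The benefit is precision and protection against chance imbalance. Its size rests on a correlation that the documents do not give. On a single change score at d = 0.5 and 30 v 30, the gain is 2 to 4 percentage points of power for r = 0.2–0.3 and about 12 points for r = 0.5. If GFR is unrelated to change, the gain is nil and the loss is a few degrees of freedom.

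**What to change.** 1. **Covariate.** While the analyses are being revised as the Update section says, and before unblinding, pre-specify the qualifying eGFR as a covariate together with its interaction with time in the RS-2 v placebo analysis, at least for PCS and IS. An equivalent route is to model the week 8 and week 16 values, adjusted for eGFR and for the baseline value of the outcome. A GFR main effect alone would not do.
2. **Data.** Record the qualifying value and its date in the trial database. The value must exist for the criterion to have been applied, but the article does not describe its capture.
3. **Erratum.** Write the unit as ml/min/1.73 m².
4. **Optional.** If a new RS-2/placebo allocation list is made now that exercise has been dropped, stratify it by stage 3 v stage 4. The article does not say that a new list is planned.

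Cost: about one degree of freedom per time contrast, extraction of one value per patient from existing records, and one corrected unit. No new visit or assay is needed.

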#### Exclusionary criteria

Patients are excluded if they have any of the absolute contraindications to exercise as defined by the American College of Sports Medicine (ACSM) [18]; if they have received a kidney transplant; if they have received antibiotic therapy within the previous month, or if they have taken prebiotic or probiotic supplements within the month prior to the start of the study [19]; if they have any gastrointestinal condition that prohibits their use of resistant starch [19], or if they have been involved in a structured exercise program (i.e., exercising 3 days per week at a moderate intensity for at least the previous 3 months). Individuals who are pregnant are also excluded from this study.

### Recruitment

A member of the research team (EE), has been given access to the patient database at the local nephrology practice participating in this study. She screens the list of patients and approaches those who meet the eligibility criteria for the study at their next scheduled appointment. While patients are waiting to see their nephrologist, she explains the details of the study to them. If they indicate a willingness to participate, she gives them the medical history form to take into the appointment with them. If the nephrologist approves of the patient’s participation in the study, EE obtains informed consent from the patient and enrolls them into the study at that time. Individuals are free to withdraw from the study at any time as stated in the IRB approved consent form. Individuals who experience adverse reactions from taking the supplement will be removed from the study without penalty.

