### Interventions

#### Nutrition protocol

Participants are randomized to receive a supplement of either resistant starch (intervention) or waxy cornstarch (control). The study dietitian (DC) is the only “unblinded” member of the research team, and is responsible for providing the correct supplement to participants, without revealing the randomization scheme to other team members or participants. At the completion of the study, DC reveals the contents of the supplement to the participant. The resistant starch is composed of 40% digestible starch and 60% resistant starch and is provided as Hi-Maize® 260 resistant starch (Hi-Maize 260, Ingredion, Bridgewater, NJ). The control is Amioca® corn starch (AMIOCA, Ingredion, Bridgewater, NJ), is nearly completely digestible. For week 1, the dose of supplements is 15 g/day. The dose is then increased to 33 g/day for weeks 2–16. Participants are instructed to blend their supplement into commonly consumed foods/beverages such as yogurt, soups, oatmeal, coffee, or juice. This daily dose was selected to provide a minimum of 30 g resistant starch/day as previously reported by Sirich et al. [9], and allow for the 10% variability in the sachet weight as determined by the commercial packing company. Sirich et al. [9] utilized a similar protocol with good gastrointestinal tolerance. Participants are provided with dosing suggestions and recipes to promote good compliance. Supplements are provided to participants as daily doses in sachets labeled as either “Supplement 1” or “Supplement 2”. Participants are issued half of their daily doses of supplement at visit 2, and the remaining daily doses of supplement are provided at visit 3. Participants are instructed to return any unused supplement at the completion of the study. A research assistant contacts the subjects biweekly during the study to determine if the subject had experienced any complications with consuming the supplement and to encourage compliance. Three-day food records are administered at baseline, and week 16 and entered into Food Processor software (ESHA) for nutrient analysis -to assess between-group differences in dietary intake of nutrients which may impact upon renal function (i.e. protein, potassium, phosphorus).

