### Sample size estimates

A study investigating the effects of aerobic exercise on inflammation reduction [24] demonstrated effect sizes (Cohen’s *d*) varying between .40 and .77 for IL-6 and IL-10 and their ratio, which would be considered a medium to large effect. Few studies have investigated the effect of prebiotic supplements on inflammation, though similar magnitude effect sizes were reported for a prebiotic supplement intervention on changes in free circulating uremic solutes indoxyl sulfate and p-cresol sulfate, key indicators of adverse outcomes of CKD [9], though those changes were not found to be significant in that small sample study. Based on these studies, we anticipate medium effect sizes, and with power set at .80, and alpha set at .05, a sample size of 60 (15 per group) is predicted to be sufficient for detecting significant two-way interactions specified in the statistical analysis section. To account for any dropouts from the protocol, missing data will be addressed through multiple imputation, and results of all analyses averaged over multiple imputed datasets. All variables in the analysis will be examined for assumptions for all statistical tests. Data will also be examined in a per-protocol analysis, using only data from participants in all groups who completed 70% or more of their assigned exercise sessions and/or supplement use and who provided outcome data on the relevant variables.

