## Discussion

The purpose of the study is to examine the effect that 16 weeks of supplementation with the prebiotic, RS-2, has on the composition of the microbiota of a sample of stage 3–4 CKD patients. In addition, we will be monitoring the impact of this prebiotic on the levels of key uremic toxins (PCS & IS), markers of inflammation (CRP, TNF-a, IL6,IL10, MCP1), oxidative stress (MDA and 8-isoprostanes F2a,) and some cardiovascular parameters (arterial stiffness and blood pressure) that are known to impact upon the development of CVD. The potential additive effect of 16 weeks of moderate intensity aerobic exercise on the aforementioned variables will also be explored. Since many of the previous studies performed with RS-2 supplementation have been completed with ESRD patients, this study is one of the first to examine the impact of this supplement on the most prevalent stages of kidney disease, stage 3 & 4 [1].

The success of this protocol depends upon the adherence to two behavioral interventions, namely nutritional supplementation with RS-2 and aerobic exercise training for those randomized to the exercise groups. To enhance compliance to the nutritional aspects of the study, all participants have individual counseling sessions with the study dietitian to review various strategies to consume the product. At two-week intervals during the study, a research assistant is tasked with attempting to contact the participants to determine if there are any concerns with taking the supplement. If there are any such issues, the registered dietitian is informed and the issue is addressed with the participant as soon as it is feasible.

The inclusion of supervised exercise training is a strength of the study [25]. There is some evidence that exercise training alone has a favorable effect on the composition and function of the microbiota in some individuals [26, 27]. This information has not been previously examined in persons with CKD who are known to have a dysfunctional microbiota [28, 29]. Having participants directly supervised during each training session ensures that participants are given the guidance that they need to successfully complete their prescribed exercise training [25]. This also builds in a sense of accountability.

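### Removing participants who react to the supplement from the study, not only from the supplement, ends outcome collection that the intention-to-treat analysis needs and leaves imputation to fill the gap

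*Protocol article*

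**What the plan says.** All references are to the protocol article.

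- **Recruitment:** "Individuals who experience adverse reactions from taking the supplement will be removed from the study without penalty". The sentence follows the statement of the right to withdraw and is separate from it. It sets no severity threshold and does not mention later visits or samples.
- **Statistical analyses:** "An Intention-To-Treat design will be used in this study".
- **Sample size estimates:** "To account for any dropouts from the protocol, missing data will be addressed through multiple imputation". No missingness assumption is given, and removals for reactions are not handled separately. A per-protocol analysis is planned as well, "using only data from participants in all groups who completed 70% or more of their assigned exercise sessions and/or supplement use".
- **Nutrition protocol:** for the active product, "The resistant starch is composed of 40% digestible starch and 60% resistant starch"; the control "is nearly completely digestible". On tolerance, a cited study "utilized a similar protocol with good gastrointestinal tolerance". No reaction or removal rate is given for either arm.
- **Discussion:** when a participant has a problem with the supplement, "the registered dietitian is informed and the issue is addressed with the participant". Removal is not mentioned there.
- **Update (COVID-19):** the exercise component is dropped, the main comparison becomes prebiotic against placebo over three time points, and the rest of the protocol, including the removal rule, stays in force.
- **Follow-up testing:** blood and vascular measures are repeated at weeks 8 and 16; stool is collected again only after week 16.

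**The concern.** Intention-to-treat rests on seeking the outcome from everyone randomised, whether or not they keep taking the product. The Recruitment rule ties two separate events together: the end of supplement use and the end of follow-up. The trigger is a reaction to the assigned product, so it occurs after randomisation and may depend on the arm. Because the rule covers everyone who reacts, almost no outcome data would exist from participants after a reaction. An imputation model would then have little to learn from except those who tolerated the product.

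At stake is the RS-2 versus placebo comparison, which is now the main one. The primary result could drift towards the effect in tolerators while carrying the intention-to-treat label. An analysis plan written later cannot repair this, because the samples will not have been taken.

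**Working it through.** The plan gives no figure on this point, so there is nothing to reproduce. The total of 60 does not enter the argument, except that an equal two-arm split gives the 30 per arm used below. Removal rates and responses are assumptions, shown over a range.

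**1. Formula.** Let q be the fraction of the RS-2 arm removed, δ the effect in those who stay, and ε the effect that would have been seen in those removed. Take removal in the RS-2 arm only.

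- All-randomised effect = (1 − q)δ + qε
- Missing-at-random imputation from those who stay estimates about δ
- Bias = q(δ − ε)

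**2. No effect after stopping (ε = 0).** Relative overstatement = 1/(1 − q) − 1.

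| q | All-randomised effect | Overstatement |
|---|---|---|
| 10% | 0.90δ | 1/0.90 − 1 = 11% |
| 15% | 0.85δ | 1/0.85 − 1 = 18% |
| 20% | 0.80δ | 1/0.80 − 1 = 25% |

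**3. Half the effect kept (ε = δ/2).** At q = 20% and δ = 0.50 SD, the all-randomised effect is 0.8 × 0.50 + 0.2 × 0.25 = 0.45 SD. The overstatement is 0.05/0.45 = 11%. At q = 10% it is 0.025/0.475 = 5%.

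**4. Same response (ε = δ).** Bias = q × 0 = 0 at any removal rate.

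**5. Check by simulation.** Assumed: 30 per arm, baseline correlation 0.5, δ = 0.5 SD, 10 proper normal imputations under missing at random, 1,500 runs.

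| Removed from RS-2 | Effect in removed | Effect with full follow-up | Effect after imputation |
|---|---|---|---|
| 10% | 0 | 0.448 | 0.499 |
| 20% | 0 | 0.400 | 0.502 |
| 10% | 0.5 | 0.502 | 0.502 |
| 20% | 0.5 | 0.503 | 0.502 |

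This agrees with steps 2 and 4.

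**6. No treatment effect.** In step 2 the bias is proportional to δ, so it vanishes when δ = 0. A false positive needs another mechanism. Suppose removed participants would have had outcomes 1 SD worse whatever their arm, with removal fractions p1 (RS-2) and p0 (placebo). Then bias = (p1 − p0) × 1 SD, with standard error √[1/(30(1 − p1)) + 1/(30(1 − p0))].

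- 20% v 20%: bias 0, two-sided type I error 0.05
- 20% v 10%: bias 0.10 SD, SE 0.281, type I error 0.065
- 30% v 10%: bias 0.20 SD, SE 0.291, type I error 0.106

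Bias therefore needs removed participants to differ from those who stay, together with removal that is unequal between the arms (as in steps 2, 3 and 6) or a difference that is not the same in both arms.

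**The case against.** **The rule may be consent language.** It sits in the recruitment paragraph beside the right to withdraw and promises no penalty, so it could be participant-protection wording in a condensed article. The Discussion suggests that not every problem ends in removal. This is fair, and it is a reason to reconcile the sections. Still, the sentence is phrased as something that will happen, is distinct from voluntary withdrawal, and the Update leaves it standing.

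**A reader might infer that the rule contradicts intention-to-treat.** The text does not go so far. Nowhere are removed participants excluded from analysis; imputation keeps them in the set as randomised, and the adherent-only analysis is separate. What is weakened is follow-up, not the definition of the analysis set.

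**A reader might infer that missingness will differ by arm and that the bias favours RS-2.** Neither is documented. The rule applies to both arms, no rates are given, gastrointestinal conditions that rule out resistant starch are excluded at entry, week 1 uses a lower dose, and good tolerance is cited. The difference in digestibility makes imbalance plausible, no more. Missing at random is likewise the usual default for imputation rather than something the article states, and the imputation model may properly be left to an analysis plan.

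**A reader might infer that everyone who reacts lacks all follow-up data.** A participant who reacts after week 8 already has week-8 blood and vascular measures, which inform the imputation. No week-8 stool is planned for anyone.

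**A reader might add a loss-of-power argument.** It does not hold in the scenario illustrated. For d = 0.5, 30 v 30 gives power 0.478. Losing 20% of one arm gives 30 v 24 and 0.433. But if the removed have no effect, following everyone gives d = 0.40 at 30 v 30 and about 0.33. Full follow-up is worth having for validity, not for power.

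**Conclusion.** The point stands as a weakness in follow-up. As written, the rule ends outcome collection after a reaction to the assigned product, which undermines the intention-to-treat aim and does not sit well with the Discussion. The missing values would be imputed, most likely from tolerators.

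The possible size is an overstatement of 11% to 25% at 10% to 20% removal. This rests on three assumptions: removal in the RS-2 arm only, no effect after stopping, and missing-at-random imputation. It shrinks if some effect persists and is nil if removed participants respond like the others. The documents fix neither the direction nor the amount, so the supportable conclusion is that the RS-2 effect may be biased. What is certain under the rule is the loss of data that could have been collected at visits already scheduled.

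**What to change.** Reconcile Recruitment, Statistical analyses, Sample size estimates and Discussion so that stopping the supplement and stopping follow-up are two separate events. When the supplement is stopped remains a clinical decision and is not judged here.

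- Seek the remaining scheduled outcomes from every randomised participant unless consent is withdrawn: week-8 and week-16 blood and vascular measures, and the week-16 stool sample.
- Analyse these data as randomised.
- Report by arm the number removed or off supplement, with timing and reason.
- Where data are still missing after a reaction, add a sensitivity imputation that does not assume missing at random, either based on the placebo arm or delta-adjusted.

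The cost is an IRB amendment, revised consent wording and some visits by participants no longer taking the supplement. No new visits are needed. The change has to be made while participants are still being followed, since samples not taken cannot be recovered.
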